## Abstract

**Background:**

Although the efficacy of zoledronic acid in postmenopausal women with breast cancer has been suggested, the underlying mechanism has not been fully clarified. Therefore, which patients may benefit from zoledronic acid and the optimal frequency of zoledronic acid administration are unclear. This study evaluates the effects of zoledronic acid on the tumor response in postmenopausal women with breast cancer and explores the relationship between its efficacy and γδ T cells.

**Methods/design:**

This study is an open-label, multi-institutional, single-arm, phase II clinical trial. Zoledronic acid will be administered once during preoperative hormonal therapy with letrozole for 24 weeks in postmenopausal women with Estrogen Receptor (ER)-positive , Human Epidermal Growth Factor Receptor 2 (HER2)-negative, clinical T1 or T2 N0M0 breast cancer. The primary endpoint is the objective response rate measured by MRI at 12 and 24 weeks. The secondary endpoints are the associations between the frequency of Vγ2Vδ2 T cells before the administration of zoledronic acid and the objective response, the association between the frequency of Vγ2Vδ2 T cells and the Preoperative Endocrine Prognostic Index score, and the association between the frequency of Vγ2Vδ2 T cells and Ki67 (MIB-1 index).

**Discussion:**

This study is designed to determine the add-on effect of zoledronic acid during preoperative hormonal therapy and to investigate the changes of the frequency of Vγ2Vδ2 T cells after the administration of zoledronic acid to explore the potential mechanism of zoledronic acid in breast cancer patients.

**Trial registration:**

This trial was registered at the UMIN Clinical Trials Registry as UMIN000008701.

## Background

According to the 2008 National Breast Cancer Registry Report [1], more than half of breast cancers are Estrogen Receptor (ER)-positive, Human Epidermal Growth Factor Receptor 2 (HER2)-negative, less than 5 cm in diameter and negative for lymph node metastasis. Nevertheless, treatment with paclitaxel and anthracycline-based combinations as an adjuvant therapy in ER-positive, HER2-negative patients is less effective [2].

Hormonal therapy for early breast cancer has been shown to be effective [3]. Anastrozole is as effective as tamoxifen as a neoadjuvant treatment in postmenopausal women [4,5]. Letrozole is also more effective than tamoxifen as a preoperative treatment in postmenopausal patients with ER- and/or Progesterone Receptor (PgR)-positive primary breast cancer, although the response rate of 55% [6] is suboptimal.

Recently, the addition of zoledronic acid to adjuvant endocrine therapy in premenopausal women with breast cancer receiving goserelin improved disease-free survival and reduced the risk of disease-free survival events overall [7]. Moreover, the rates of both disease-free survival and overall survival were improved by the addition of zoledronic acid in postmenopausal patients [8,9].

Zoledronic acid appears to be efficacious in patients with early breast cancer [7-9] and in those with low levels of estrogen or a deficiency of estrogen [7-9] after menopause or oophorectomy and who were receiving hormonal therapy [7,8].

The mechanism of the efficacy of zoledronic acid seems to be through direct anti-tumor effects [10]. Many theories and hypotheses have been presented on the mechanisms of zoledronic acid on tumor response [11-13]. The involvement of immune cells, such as Vγ2Vδ2 T cell (also called γδ T cells), has also been suggested [14]. Zoledronic acid is one of the nitrogen-containing bisphosphonates (N-BPs). N-BPs, such as zoledronic acid and pamidronate, inhibit farnesyl diphosphate synthase, and its upstream metabolite diphosphomonoesters (e.g., isopentenyl diphosphate) accumulate in tumor cells. Then, Vγ2Vδ2 T cells specifically recognize and lyse the sensitized target tumor cells that bear or express antigenic substances [15,16]. The activated Vγ2Vδ2 T cells also secrete cytokines, such as interferon-γ (IFN-γ) [17]. Although it was demonstrated that the frequency of γδ T cells in peripheral blood was increased and that an acute-phase reaction occurred after treatment with pamidronate [18], the causal relationship between the function of γδ T cells and the efficacy of pamidronate has not been elucidated.

The hypothesis in this study is that zoledronic acid will elicit an anti-tumor effect in patients with early breast cancer who have a high frequency of γδ T cells in the peripheral blood. In addition, the therapeutic roles of γδ T cells might be determined by measuring body temperature and IFN-γ production because γδ T cells secrete inflammatory cytokines in response to antigenic stimulation through their T cell receptors. The aim of this study is to examine the mechanism underlying the add-on effect of zoledronic acid and to determine whether the initial frequency of γδ T cells is related to the objective response rate of patients with early breast cancer who receive hormone therapy with zoledronic acid.

### Objectives

The main objective of this study is to examine the add-on effect of zoledronic acid in the treatment of postmenopausal women with ER-positive, HER2-negative breast cancer who receive preoperative hormonal therapy by letrozole. Other objectives are as follows: the determination of the frequency of Vγ2Vδ2 T cells in peripheral blood before the administration of zoledronic acid, the analysis of the associations between the frequency of Vγ2Vδ2 T cells before the administration of zoledronic acid, the objective response, the association between the frequency and Preoperative Endocrine Prognostic Index score, and the association between the frequency and Ki67 (MIB-1 index).

## Methods/design

### Study design

This study is an open-label, multi-institutional, single-arm, phase II clinical trial. A total of 75 women will be enrolled after they give written informed consent. The study was approved by the ethical committee at Kyoto University on October 18, 2012 (C-646) and will be approved by the ethical committees at the participating hospitals prior to study initiation at each site. The study protocol complies with the Helsinki declaration [19] and the Ethics Guidelines for Clinical Research of the Ministry of Health, Labor, and Welfare [20]. This study was registered with the UMIN Clinical Trials Registry as UMIN000008701 (http://www.umin.ac.jp/ctr/index.htm). An additional study to investigate tumor infiltration with γδ T cells at baseline, 12 weeks and 24 weeks was also approved by the ethical committee at Kyoto University on June 1, 2013 (E1723).

### Eligibility criteria

Women will be included in the study if they meet the following criteria: have primary cT1-2, N0M0 breast cancer; histologically confirmed invasive ductal cancer; ER-positive and HER2-negative (i.e., as determined by either immunohistochemistry (IHC) or by FISH/DISH (fluorescence *in situ* hybridization/Dual Color *in situ* Hybridization)) breast cancer; low levels or a deficiency of estrogen (i.e., women aged 60 years or older that have been postmenopausal for more than 4 years or have had a post-bilateral oophorectomy); no prior treatment for breast cancer; measurable disease on enhanced MRI within 6 weeks prior to study entry; an Eastern Cooperative Oncology Group (ECOG) performance score of 0 or 1; are within the age range of 20 to 75; have adequate renal function with a Ccr (Cockcroft-Gault) > = 30 mL/min; and have adequate hepatic function with serum bilirubin < = 2.0 and AST/ALT < = 100.

Women will be excluded if they have: hyperparathyroidism that requires management; uncontrolled diabetes mellitus; diseases that require continuous management with systemic corticosteroids; dental and/or periodontal disease that requires invasive treatment after enrollment; currently active or past malignancies within the past five years; prior bisphosphonate therapy, if they have undergone hormone replacement therapy within 7 days prior to enrollment; are hypersensitive to contrast materials for MRI; or used other investigational drugs within 28 days prior to enrollment.

### Intervention

Participants will take 2.5 mg/day of letrozole orally within 7 days of enrollment in the study. Participants will receive a single-drip injection of zoledronic acid on day 28. The dose of zoledronic acid will be reduced when the participants demonstrate impaired renal function (i.e., when the Ccr is equal to or less than 60 mL/min) according to Table 1. A single administration of zoledronic acid is expected to be effective because frequent zoledronic acid treatments lead to a decrease in blood Vγ2Vδ2 T cell levels [14]. Cytokines such as IL-2 are not used in combination with zoledronic acid because patients with early breast cancer without any previous treatment have a potential to restore immune responses against tumor antigens without administration of cytokines such as IL-2. Participants will take letrozole every day for 24 to 26 weeks until they have a mastectomy as a part of routine medical care. The study treatment will be terminated upon disease progression, episodes of serious adverse events, or in patients for whom zoledronic acid cannot be administered within 35 days of starting letrozole treatment.

**Table 1 Tab1:** **Dose of zoledronic acid**

	**Ccr (mL/min)**			
	**>60**	**50 - 60**	**40 - 49**	**30 - 39**
Dose of zoledronic acid	4 mg	3.5 mg	3.3 mg	3.0 mg

### Measurements

Patients will be evaluated clinically and through laboratory testing, radiological testing and pathological testing, according to Table 2.

**Table 2 Tab2:** **Trial schedule**

**Protocol treatments and assessments**		**Pre-enrollment**	**Week 1**	**Week 4**	**Week8**	**Week 12**	**Week 16**	**Week 20**	**Week 24**	**Mastectomy**
**Protocol treatments**	**Letrozole**									
	**Zoledronic acid**			↓						
Demographics, current medications, dental examination		○								
Physical examination		○		○^1^						
Complete blood count, blood biochemical test, bone metabolism markers		○		○^2^	○		○		○	
Enhanced MRI, tumor markers		○				○			○	
Palpation, ultrasound examination		○		○	○	○	○	○	○	
Vδ1+ T cells and Vδ2+ T cells in peripheral blood ^3^				○	○				○	
IFN- γ ^4^				○						
Pathological examination^5^		○			○					○
PEPI score										○

^1^Body temperature before and 4–6 hours after the administration of zoledronic acid.

^2^Bone metabolism markers that are expected.

^3^The frequency of Vδ1+ T cells and Vδ2+ T cells among CD3+ T cells in peripheral blood.

^4^IFN-γ at 4–6 hours after the administration of zoledronic acid.

^5^ER, PgR, Ki67.

The primary endpoint is the objective response rate (ORR). The ORR is defined as the proportion of the complete response (CR) and the partial response (PR) within the best overall response based on MRI evaluation. Patients will undergo tumor assessments at baseline, 12 weeks and 24 weeks by investigators using the Response Evaluation Criteria in Solid Tumors (RECIST) version 1.1 [21]. The imaging modality is restricted to MRI because MRI is superior to other modalities for the detection and staging of invasive breast cancer, and MRI measurements after neoadjuvant treatment are more highly correlated with pathological tumor size than mammography or ultrasound [22]. The secondary endpoints are the change in tumor volume, ORRs using ultrasonography or clinical assessment, breast-conserving surgery, the frequency of Vγ2Vδ2 T cells, PEPI score [23], Ki67 (MIB-1 index) and safety.

Tumor volume will be measured using MRI volumetry at baseline, 12 weeks and 24 weeks by an independent committee. The contrast-enhanced MRI will be performed according to the European Society of Breast Imaging (EUSOBI) guidelines [24]. ORRs using ultrasonography or clinical assessment will be evaluated separately by the investigators according to RECIST. A partial resection of the breast will be regarded as breast-conserving surgery after the completion of letrozole treatment.

The frequency of Vδ1^+^ T cells and Vδ2^+^ T cells among CD3^+^ T cells in peripheral blood mononuclear cells will be analyzed by two-color flow cytometry [11] and will be evaluated at baseline, 4 weeks and 20 weeks after the administration of zoledronic acid.

Peripheral mononuclear cells (PBMC) will be purified by density gradient centrifugation. For flow cytometric experiments, 2 × 10^5^ cells of PBMC in each well will be stained with mAbs. The following mAbs will be used: fluorescein isothiocyanate (FITC)-conjugated anti- Vδ1 mAbs (Thermo Scientific, Rockford, IL), Vδ2 mAbs (Beckman Coulter Inc., Fullerton, CA), anti-CD3 mAbs (BioLegend, San Diego, CA), phycoerythrin (PE)-conjugated anti-CD3, CD4, CD8, CD25, NKG2D mAbs (BD Biosciences, San Diego, CA) and FcR blocking reagent (Miltenyi Biotec GmbH, Bergisch Gradbach, Germany) will be used. The stained cells will be subjected to 2-color flow cytometry using a FACSCalibur flow cytometer (Becton–Dickinson, Franklin Lakes, NJ) and the analyses will be performed on a single sample. The serum at 5 hours after administration of zoledronic acid will be collected and subjected to ELISA for IFN-γ level using an ELISA Kit (PEPROTECH, Rocky Hill, NJ) according to the manufacturer’s instructions. The analyses will be conducted on triplicate samples.

Adverse events will be evaluated according to the Common Terminology Criteria for Adverse Events (CTCAE) version 4.0 [25].

### Data analysis

The sample size was determined using the Bayesian method based on predictive distributions [26,27]. The ORR of preoperative hormonal therapy by letrozole is estimated to be 45% [28]. The threshold ORR of 45% was used as the prespecified target value for the primary endpoint. The uniform distribution and the degenerated distribution at an expected ORR of 60% were used as the analysis prior and the design prior, respectively. The sample size of 75 is required to preserve the Bayesian power of 80% with a prespecified probability threshold of 95% to declare the treatment efficacious.

The primary statistical analysis will be performed using the Bayesian approach according to the intention-to-treat principle. The posterior beta distribution of the ORR will be calculated using the prior uniform distribution. If the posterior probability that the ORR is greater than the prespecified target value of 45% exceeds a prespecified probability threshold of 95%, the treatment will be considered efficacious.

A subset analyses for the ORR based on MRI and tumor volume using MRI volumetry according to (a) equal and greater or less than the median of the frequency of Vγ2Vδ2 T cells before the administration of zoledronic acid, (b) equal and greater or less than the median of IFN-γ at 5 hours after the administration of zoledronic acid and (c) presence of fever and/or flu-like symptoms, are planned. Exploratory subgroup analyses for the frequency of Vγ2Vδ2 T cells according to (a) equal and greater or less than a body mass index of 25, (b) 0, 1–3, or over 3 of PEPI score, (c) equal and greater or less than 14 of Ki67, (d) equal and greater or less than the median of IFN-γ at 5 hours after the administration of zoledronic acid and (e) presence of fever and/or flu-like symptoms, are also planned.

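### The stated inputs do not make 75 patients the requirement for 80% Bayesian power: they give 85.5% at 75, and 69 patients are enough for 80%

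*Protocol article*

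**What the plan says.** The protocol article, under Data analysis, gives the full recipe for the sample size.

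- Target: "The threshold ORR of 45% was used as the prespecified target value for the primary endpoint".
- Priors: uniform for the analysis; for the design, "the degenerated distribution at an expected ORR of 60% were used as the analysis prior and the design prior, respectively".
- Analysis: "The posterior beta distribution of the ORR will be calculated using the prior uniform distribution".
- Success rule: "If the posterior probability that the ORR is greater than the prespecified target value of 45% exceeds a prespecified probability threshold of 95" per cent, the treatment is declared efficacious.
- Result: "The sample size of 75 is required to preserve the Bayesian power of 80% with a prespecified probability threshold of 95" per cent.

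Under Study design the same number is the number enrolled: "A total of 75 women will be enrolled after they give written informed consent". On the analysis set, Data analysis says: "The primary statistical analysis will be performed using the Bayesian approach according to the intention-to-treat principle". The article mentions no drop-out allowance.

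**The concern.** When the design prior is a single point, Bayesian power is simply the binomial probability, at that point, of reaching the smallest successful count. Nothing needs to be assumed or simulated, so anyone can check the sentence. It fails the check by more than rounding: 5.5 percentage points in power, or 6 patients in size.

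The sentence is the only statement of the operating characteristics of the primary analysis. A reader who takes it at face value will misjudge the chance of success the trial was given, will not know that 41 of 75 is the cut-off, and cannot tell whether 75 came from this calculation, from another one, or from this one plus an allowance. The article describes the trial as ongoing, so the figures can still be set straight before the result is known.

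**Working it through.** **Inputs** (all from Data analysis): target 0.45; analysis prior Beta(1, 1); design prior a point mass at 0.60; success if Pr(ORR > 0.45 | data) > 0.95; n = 75; stated power 80%.

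**Step 1, cut-off.** With r responders among n, the posterior is Beta(1 + r, 1 + n − r). The cut-off is the smallest r for which the probability above 0.45 exceeds 0.95. At n = 75:

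- r = 40: Beta(41, 36) gives 0.9265, not a success.
- r = 41: Beta(42, 35) gives 0.9535, a success.

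**Step 2, power.** P(X ≥ 41 | n = 75, p = 0.60) = 0.8554, against the stated 0.80.

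**Step 3, false success.** P(X ≥ 41 | n = 75, p = 0.45) = 0.0590.

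**Step 4, the size that gives 80%.** Repeating steps 1 to 3 for other n:

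| n | cut-off | posterior at cut-off | power at 60% | false success at 45% |
|---|---|---|---|---|
| 62 | 35 | 0.9646 | 0.7593 | 0.0464 |
| 63 | 35 | 0.9535 | 0.8026 | 0.0600 |
| 64 | 36 | 0.9643 | 0.7714 | 0.0465 |
| 66 | 37 | 0.9641 | 0.7829 | 0.0466 |
| 68 | 38 | 0.9640 | 0.7937 | 0.0466 |
| 69 | 38 | 0.9533 | 0.8312 | 0.0596 |
| 70 | 39 | 0.9638 | 0.8040 | 0.0467 |
| 75 | 41 | 0.9535 | 0.8554 | 0.0590 |

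Power moves in a saw-tooth because the cut-off is a whole number. It first reaches 80% at 63, falls below at 64, 66 and 68, and is at or above 80% at every size from 69 (checked up to 300). Even the cautious criterion, a size beyond which power never drops below 80% again, gives 69 and not 75.

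**Step 5, can another reading return the stated pair?** At n = 75:

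- Jeffreys prior: cut-off 41, power 85.5%.
- Posterior threshold of 97.5%: cut-off 43, power 72.4%.
- Exact one-sided 5% binomial test: cut-off 42, power 79.6%.

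The normal approximation gives 68 patients (one-sided 5%) or 86 (one-sided 2.5%). Inflating for losses can also land on 75: 69 / 0.92 = 75, and 68 × 1.1 = 74.8. None of these is what the article describes.

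**Step 6, conditional check on missing MRI.** Suppose k of the 75 patients have no usable response assessment. If they count as non-responders, and the others respond at 60%, power is P(X ≥ 41 | 75 − k, 0.60). If they are left out, the cut-off is recalculated for 75 − k.

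| k | counted as non-responders | left out |
|---|---|---|
| 0 | 85.5% | 85.5% |
| 1 | 82.3% | 82.3% |
| 2 | 78.6% | 84.8% |
| 5 | 64.5% | 80.4% |

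If 60% is already the rate among all enrolled patients, power stays at 85.5% whatever k is. The middle column corresponds to an all-enrolled rate of 0.60 × 73/75 = 58.4% at k = 2 and 0.60 × 70/75 = 56.0% at k = 5. The article gives no value for k; these are illustrations.

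**The case against.** The best defence is that the error is on the safe side. With complete data the trial has more power than claimed, and if 80% is read as a floor, 75 meets it. That stands: the size is not inadequate. It does not rescue the sentence, which calls 75 required when 69 would do.

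A second defence is that the surplus of six patients is a drop-out allowance kept in the full protocol, which an article may omit. That is plausible, and the absence of such a detail is not the complaint. The complaint is that the printed sentence attributes 75 to the power target alone.

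Three stronger readings are tempting, and the documents do not support them.

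- A reader might infer that the intention-to-treat analysis is underpowered because two non-evaluable patients bring power under 80%. This needs two assumptions the article does not make: that such patients count as non-responders, and that 60% refers to evaluable patients only. Even then, two patients leave power only 1.4 points short of 80%.
- A reader might infer that the Intervention section produces non-evaluable patients by ending study treatment in "patients for whom zoledronic acid cannot be administered within 35 days of starting letrozole treatment". That rule ends treatment. It does not say that MRI assessment stops, so these patients may still have a response recorded.
- A reader might infer a conflict between cut-offs of 41 and 42, because 42/75 gives about 80% power. No cut-off of 42 appears anywhere in the article. The written rule settles 41/75 as a success without ambiguity.

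**Conclusion.** The stated power and required size are wrong on the article's own inputs. At 75 patients the rule means at least 41 responders, with power 85.5% instead of 80%, and 80% power is held from 69 patients (first reached at 63). This rests on no assumption beyond those printed under Data analysis and a binomial count of responders with complete data.

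The trial is not too small and the success rule is clear, so the primary conclusion is not endangered. The false-success probability of 5.9% is not a breach either: the article sets a posterior threshold and promises no 5% error rate. It is a figure the reader should have. The possible loss of power from missing MRI is a conditional note only: 82.3%, 78.6% and 64.5% with one, two and five such patients under the non-responder assumption, and no loss if 60% is the all-enrolled rate.

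The correction is worth making because this is the primary design statement, but it is a correction of reporting.

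**What to change.** Replace the sample-size sentence with wording such as: n = 75; success if at least 41 patients respond; Bayesian power 85.5% at an ORR of 60%; false-success probability 5.9% at an ORR of 45%; 69 patients suffice for power of at least 80%. If 75 includes an allowance for drop-out, say so and give the rate. Add one clause stating whether the 60% is expected among all enrolled patients or only among those with a usable MRI; in the second case, give the power for the assumed number of non-evaluable patients.

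Leave the 95% posterior threshold unchanged. Raising it to reach a power nearer 80% would alter a clear prespecified success criterion in an ongoing trial.

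The cost is a few lines of text, with no extra patients and no change to the analysis. The one drawback is that, if 60% applies to evaluable patients only and the others count as non-responders, the power to be reported may fall below 80%.

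### MRI response and tumour volume are related to Vγ2Vδ2 T-cell frequency and IFN-γ only through median splits, which wastes information if the relation is graded

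*Protocol article*

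**What the plan says.** The Background puts forward the hypothesis that "zoledronic acid will elicit an anti-tumor effect in patients with early breast cancer who have a high frequency of γδ T cells" and sets the aim "to determine whether the initial frequency of γδ T cells is related to the objective response rate". The abstract (Methods/design) lists the association of pre-dose frequency with objective response among the secondary endpoints, and the Objectives section repeats it. Neither names a method.

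The Data analysis section names three subset analyses for MRI response and MRI tumour volume:

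- T-cell frequency: "equal and greater or less than the median of the frequency of Vγ2Vδ2 T cells before the administration of zoledronic acid"
- IFN-γ: "equal and greater or less than the median of IFN-γ at 5 hours after the administration of zoledronic acid"
- fever and/or flu-like symptoms, present or absent

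It then lists exploratory analyses in which T-cell frequency is the quantity compared, across groups formed by BMI, PEPI score, Ki67, IFN-γ and fever. Frequency itself is not said to be split there.

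Both markers are continuous. Frequency is a share of CD3+ cells by flow cytometry, and IFN-γ is a serum level by ELISA (Measurements).

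**The concern.** A median split gives a woman just above the cut the same value as the woman with the highest frequency, and separates her fully from the woman just below. The cut is set by whichever women enrol. The article speaks of a high frequency but gives no threshold, and nothing in it ties the sample median to biology.

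What is at stake is the mechanistic aim. The trial is sized for the primary response-rate test alone, so the marker analyses have no power to spare. If they are run only as halves, a real graded association is easier to miss, and a null result would say little about the proposed mechanism.

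**Working it through.** **The plan's own figure.** The planned size is 75 women (Study design). Per the Data analysis section, the rate to beat is 45%, the analysis prior is uniform, and the design prior puts all its mass on 60%. The stated Bayesian power is 80% with a 95% posterior threshold. With r responders the posterior is Beta(1 + r, 1 + 75 − r). The smallest r with P(ORR > 0.45) > 0.95 is 41 (posterior 0.953). Under that rule, power at a true rate of 60% is 85.5%, and the chance of success at 45% is 5.9%. So 75 meets the 80% target with some margin; the calculation does not return exactly 80%. This has no bearing on the present point. The article states no power for the marker analyses.

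**Assumptions.** The article gives neither the distribution of the markers nor the shape or size of their relation to response. Assumed here: a normal marker (such as log frequency), a logit-linear relation, odds ratio 1.5–2.5 per SD, overall response rate 45% or 60%, two-sided 5% test, all 75 patients evaluable.

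**Large-sample loss.** The correlation of a normal variable with its own median split is √(2/π) = 0.798. Relative information is its square, 2/π = 0.637, a loss of 36%. Then 75 × 0.637 = 47.7, so 75 patients act like about 48.

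**Loss at n = 75, response.** 20,000 simulated trials per scenario, score test:

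| OR per SD | ORR 60%: continuous | ORR 60%: split | ORR 45%: continuous | ORR 45%: split |
|---|---|---|---|---|
| 1.5 | 38% | 29% | 39% | 30% |
| 1.75 | 61% | 47% | 63% | 48% |
| 2.0 | 78% | 62% | 80% | 64% |
| 2.5 | 94% | 82% | 95% | 83% |

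The efficiency of the split, as the ratio of (mean χ² − 1), runs from 0.66 to 0.71, a loss of 29–34%.

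At OR 2.0 and overall ORR 60%, the halves have response rates of 72.4% and 47.6%, a gap of 24.8 points. With 37 per half, 80% power needs a gap of about 31–32 points (lower half at 40–50%).

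**Tumour volume.** Fisher-z power is Φ(atanh(ρ)·√72 − 1.96).

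- Continuous, ρ = 0.30: atanh = 0.310, × 8.485 = 2.63, power 75%.
- Split, ρ = 0.30 × 0.798 = 0.239: atanh = 0.244, × 8.485 = 2.07, power 54%.
- Patients needed for 80% power: about 85 continuous, 135 split.

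**Where the advantage disappears.**

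- True step at the median (response 75% above, 45% below): split 72%, linear term 57%.
- Log-normal marker entered untransformed, OR 2.0 per SD of the log: linear term 57% against split 62% at ORR 60%; 64% against 64% at ORR 45%.

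**The case against.** The strongest case on the other side has four parts.

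- **The splits are called subset analyses.** The article never says they are the method for the association endpoints, and a condensed article may leave the model to a fuller document. This stands in part: an unseen plan may contain a continuous analysis. But the published text does fix a concrete method for these outcomes, and it suits the stated aim poorly.
- **The hypothesis speaks of a high frequency, which a threshold could fit.** This stands as a limit on the size of the loss. Nothing in the article places a threshold at the median, however.
- **The work is hypothesis-generating.** The Discussion concedes that a single arm cannot tell a prognostic role of T-cell frequency from one tied to zoledronic acid, and no significance test is named for the subsets. This stands and lowers the stakes. It is no reason to discard information.
- **A prespecified median prevents a data-driven cut.** True, but a prespecified continuous model prevents it as well.

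A reader might infer that the whole γδ T-cell question is examined only by median splits. The text does not support that: the PEPI, Ki67, BMI and fever comparisons use frequency as the outcome, with no split of it stated. A reader might also infer that tumour volume is categorised, or that all the cut-points depend on the sample. Volume is an outcome and is never categorised, and BMI 25, Ki67 14 and the PEPI groups are fixed in advance.

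**Conclusion.** The point holds for MRI response and MRI tumour volume analysed by pre-dose Vγ2Vδ2 frequency and by IFN-γ. For these, median splits are the only stated use of either marker. Under a graded relation and a roughly normal marker the cost is about 30–36% of the information, or around 16 points of power at OR 2.0 per SD (78% − 62%) and 21 points for volume at ρ = 0.30 (75% − 54%).

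It would be tempting to state the loss of a third as a fact. The article does not support that, since it gives neither distribution nor shape, and a step at the median would favour the split. The primary endpoint, its sample size and its decision rule are unaffected. This is a worthwhile, inexpensive improvement to the secondary analyses, and does not put the trial's main conclusion at risk.

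**What to change.** Specify a continuous analysis as the main one for these associations:

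- **MRI response:** logistic regression on log-transformed (or ranked) pre-dose Vγ2Vδ2 frequency, and separately on IFN-γ, reporting the odds ratio per SD with its interval.
- **Change in MRI tumour volume:** linear regression on the same scale, or Spearman correlation, with an interval.
- **Median split:** keep as already prespecified, as a supporting display.

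Fix the transformation before marker and response data are looked at together. An untransformed linear term should be avoided if the marker is skewed, since it may do no better than the split.

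The cost is a change of wording in the analysis plan, with no new patients, samples or visits. The downside is that a functional form must be chosen in advance, and some power is lost if the true effect is a step at the median.

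### The T-cell/Ki67 association, a named secondary endpoint, is analysed only by splitting patients at a fixed Ki67 of 14; keeping Ki67 continuous would use the same data better

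*Protocol article*

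**What the plan says.** All references are to the protocol article.

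- **Endpoint.** The abstract lists among the secondary endpoints "the association between the frequency of Vγ2Vδ2 T cells and Ki67 (MIB-1 index". The Objectives section repeats this association as an aim. The Measurements section also lists Ki67 in its own right: "PEPI score [23], Ki67 (MIB-1 index) and safety".
- **Ki67 data.** In Table 2 the pathological examination, which footnote 5 defines to include Ki67, is marked at pre-enrollment, week 8 and mastectomy.
- **T-cell data.** T-cell frequency "will be evaluated at baseline, 4 weeks and 20 weeks after the administration of zoledronic acid". By Table 2 these samples fall at weeks 4, 8 and 24.
- **Timing of drugs.** Letrozole starts within a week of enrollment. For the second drug the Intervention section says: "Participants will receive a single-drip injection of zoledronic acid on day 28".
- **Analysis.** The one stated analysis linking Ki67 to T cells is in the Data analysis section, in a list that opens "Exploratory subgroup analyses for the frequency of Vγ2Vδ2 T cells according to". Its third item is "c) equal and greater or less than 14 of Ki67". Neither the Ki67 sample nor the T-cell sample is specified there.

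**The concern.** The trial's hypothesis concerns γδ T cells, and their relation to Ki67 is one of the few places where that hypothesis meets a tissue measurement. The article fixes the form of the analysis: two groups formed at one cut. A patient at 15 is treated like one at 60, and unlike one at 13. When the underlying relation is graded, such grouping lowers the chance of seeing it. The loss grows as the groups become more unequal, and they may well be unequal if treatment lowers Ki67.

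If the pre-enrollment Ki67 were the value split, there is a further limit. That sample precedes both drugs, so the comparison could show only a baseline correlation and nothing about Ki67 on treatment.

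What is at stake is a secondary, mechanism-oriented result. A weak or null finding from the split would be harder to interpret than it need be.

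**Working it through.** The article states no power or precision figure for this analysis, so there is none to reproduce.

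**Inputs**
- From the Study design section: "A total of 75 women will be enrolled". This number was set for the response-rate endpoint and is used here only as the number of patients available.
- Assumed: the correlation ρ between T-cell frequency and continuous (log) Ki67 at the chosen time; 0.30 as the main case, 0.20 and 0.40 as the range.
- Assumed: the share p of patients at or above 14, from 50% down to 5%.
- Assumed: approximate bivariate normality; two-sided 5% level. The article names no test, so power serves only as a yardstick for comparing methods.

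**Information kept by the split.** With c the normal quantile that leaves share p above it and φ the normal density, relative efficiency = φ(c)² / [p(1 − p)]. For p = 0.50: φ(0) = 0.399, so 0.159 / 0.25 = 0.637. The loss is 36%, and 75 × 0.637 = 47.7 effective patients.

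**Power.** Fisher z: power = Φ(atanh(r)·√72 − 1.96), with r = ρ for the continuous value and r = ρ·√efficiency for the split.
- Continuous, ρ = 0.30: atanh(0.30) = 0.3095; × 8.485 = 2.626; − 1.96 = 0.666; power 75%.
- Even split: r = 0.30 × √0.637 = 0.239; atanh = 0.244; × 8.485 = 2.071; − 1.96 = 0.111; power 54%.

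| Share at or above 14 | Information lost | Effective n of 75 | Power, split (ρ = 0.30) | Power, continuous |
|---|---|---|---|---|
| 50% | 36% | 48 | 54% | 75% |
| 30% | 42% | 43 | 50% | 75% |
| 20% | 51% | 37 | 44% | 75% |
| 10% | 66% | 26 | 32% | 75% |
| 5% | 78% | 17 | not computed | 75% |

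At ρ = 0.20 the continuous analysis has 41% power, against 28% (even split) to 17% (10% above). At ρ = 0.40 it has 95%, against 80% to 53%. The continuous analysis is ahead throughout.

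**Does adjusting for baseline Ki67 add power?** Assume a correlation of 0.30 between T cells and week-8 log Ki67, and 0.6 between baseline and week-8 log Ki67. Let b be the correlation of T cells with baseline log Ki67. The partial correlation is (0.30 − 0.6b) / [0.8·√(1 − b²)], and power uses √71 = 8.426.
- b = 0: 0.30 / 0.8 = 0.375, above the unadjusted 0.30, so power rises.
- b = 0.18: 0.192 / 0.787 = 0.244; power about 55%, below the unadjusted 75%.
- b = 0.30: 0.120 / 0.763 = 0.157; power about 27%.

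Adjustment can therefore raise or lower power. It answers a different question: Ki67 on treatment given where the patient started.

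**The case against.** The other side has several good points.

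- **The missing time point.** An article commonly leaves this to the full protocol or analysis plan, neither of which is shown. I accept this: the lack of a date is not a finding. The fixed cut is different, because the article itself sets it.
- **Exploratory label.** The split sits in an exploratory list and names no test. That is correct and keeps the point small. It does not remove it, since the abstract gives the same association secondary-endpoint status and no other analysis of it is stated.
- **Ki67 as its own endpoint.** Ki67 is also listed separately, and its summary, including change from baseline, may be set out elsewhere. A reader might infer that the fall in Ki67 is never analysed or that the baseline value goes unused. The article does not support that: an undated split could even be on the baseline value.
- **What was promised.** The abstract and Objectives speak of an association, not of a drug effect on Ki67. A reader might infer that the stated rule cannot address the endpoint at all. That is too strong, because a baseline comparison would still be an association of the kind named.
- **Limits of any fix.** There is no Ki67 sample at day 28 and no control arm. Change from pre-enrollment mixes letrozole with zoledronic acid. The Discussion already concedes that the single-arm design cannot tell whether T-cell frequency matters regardless of zoledronic acid or through it.

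What remains is the choice to dichotomise.

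**Conclusion.** The concern holds as a minor point about dichotomisation. The only stated analysis of a named secondary association uses a fixed cut at 14, and a continuous analysis of data already scheduled would be more informative. Under approximate normality the split loses about 36% to 42% of the information for shares at or above 14 between 50% and 30%. With 75 patients and ρ = 0.30, power falls from about 75% to between 54% and 32%, depending on how uneven the groups are. These figures rest on an assumed correlation and an assumed Ki67 distribution, since the article gives neither. If some patients lack a usable sample, all the power figures fall.

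Two stronger readings are tempting and not supported. One is that the split throws away most of the information: that is so only if about 20% or fewer of the patients fall on one side of 14, which the article does not show. The other is that a baseline-adjusted model is always the most powerful choice: the order changes with the correlation between T cells and baseline Ki67. The primary endpoint, sample size and decision rule are unaffected.

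**What to change.** Reword the Ki67 item in the Data analysis section along these lines:

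- **Main analysis of this association:** relate T-cell frequency before zoledronic acid to log Ki67 as a continuous value (small constant added for zeros) at week 8 and, separately, at surgery. Give the estimate with its confidence interval.
- **Reported beside it:** the same model with log pre-enrollment Ki67 as covariate, described as addressing change from the patient's own starting value and not as a device for gaining power.
- **Descriptive only:** T-cell frequency by Ki67 below 14 versus 14 or above, labelled with the time point used.
- **Interpretation:** state that any result is an association under letrozole plus zoledronic acid, because there is no control arm and no Ki67 sample at day 28.

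The cost is analysis wording only, as all three Ki67 samples are already scheduled. The small downside is that patients without the relevant post-treatment sample drop out of that model, so the number analysed should be reported for each time point.
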